### Outcome measures

The primary outcome measures are:

**Gain in EBM knowledge **measured by multiple choice questions (MCQs) that have been shown to have face/content validity in relation to course objectives and discrimination capacity in previous studies. Multiple choice questions have been developed by using questions from validated questionnaires and adapting them to the current course [4,12,13].

**Change in attitudes **towards EBM and competencies in EBM. Attitudes towards EBM will be measured by a validated questionnaire. Previously validated questions to assess attitudes towards EBM will be used [4].

**Skills competence **in applying EBM principles will be measured by *Objective Structured Clinical Examination *(OSCE). The OSCE is a well established way to assess clinical competency. In this case, EBM-skills related questions following the OSCE structure will be developed for completion electronically.

As a secondary outcome measure, we will assess the educational environment towards EBM by using a questionnaire (EBMEEM). The EBMEEM development is based on previously validated environment measurement tools in different clinical settings [14,15]. The trial will also serve to validate the tool in a larger setting. Trial participants will complete the questionnaire at the beginning and at the end of the course. Only data from the first completion (baseline) will be used for validation purposes. Data from the second administration at the end of the course will be analysed after determining the items to be included in the validated instrument. Items remaining in the validated instrument will be used to generate baseline scores for the educational environment and to monitor and compare any possible changes at the end of the trial.

#### Development of the EBMEEM tool

Using the format of previously developed tools the content of the RHL-EBM Course were adapted and included in a draft instrument that yielded 63 Likert-scale items. The items were organized around certain themes namely, learning opportunities; own learning (EBM competence); availability of leaning resources; teachers and teaching (EBM specific); supervision and support; EBM practice (EM atmosphere); and general atmosphere. After several iterations of pilot-testing involving postgraduate trainees in a number of countries and the Steering Committee, the draft instrument to be validated and used in outcome assessement was agreed upon.

Process outcomes such as the experience of the facilitators and the postgraduate trainees will be evaluated through interviews.

### Follow-up procedure

The intervention period will be 8-12 weeks. Currently, follow-up beyond the trial period is not planned mainly due to financial constraints. If funds are available a one-year assessment of the EBM educational environment will be considered.

### Data management

Data will be collected in the centres using an online data management system developed by the Geneva Foundation for Medical Education and Research (GFMER). Data management will be based at the GFMER, Geneva, Switzerland supervised and monitored by HRP/RHR and Birmingham University.

Data collection will be at baseline (before the intervention), and after completion of the intervention. Data will be recorded by online completion of data forms (MCQs) and questionnaires (attitude, educational environment).

Data entry will be monitored on a day-to-day basis and any problems with logins, missing data and queries will be resolved promptly. The system allows data export to common statistical packages for analysis. It has been agreed that the data files will be exported to an Excel file to be analyzed by the trial statistician in the Statistics and Informatics Services Team at the HRP/RHR.

### Analysis plan

Since the random allocation is by teaching units and the inferences will be made at this level, the analysis at the teaching unit will be the unit of analysis.

At each participating unit the postgraduate trainees will use the online system to enter their personal data and access the assessment questions (all) and the e-learning modules of the course (either intervention or control materials). The postgraduate trainees will complete the relevant sections at baseline and at the end of the trial period.

### Analysis plan for primary outcomes

A score for each individual by dividing the number of points obtained in a test by the maximal number of points that can be obtained will be computed. A summary measure will be obtained for each teaching unit as the mean score for all the individuals taking the test in that unit at baseline (pre-) and post-evaluation phase.

We will compare the knowledge (main outcome) between intervention and control units using analysis of covariance, with pre-test score as a baseline covariate and terms for the stratum and for the group in the model. A 95% confidence interval will be calculated for the difference in knowledge between intervention and control, based on the error term from the analysis of covariance.

We will also compute the change in knowledge as the difference between the post- and the pre-test scores for each individual. A summary measure of the gain in knowledge for each teaching unit will be computed as the mean gain in knowledge. We will compare the gain in knowledge between intervention and control units using analysis of variance, with terms for the stratum and for the group in the model. A 95% confidence interval will be calculated for the difference in gain in knowledge between intervention and control, based on the error term from the analysis of variance.

It is anticipated that in some countries there will be existing formal or informal postgraduate training activities on EBM. These will be reported in the survey of EBM activities that will be conducted before the trial. If data permits a stratified analysis based on the presence or absence of additional basic EBM courses will be conducted. However, it is acknowledged that the study may be underpowered to provide a definitive answer according to the two strata.

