### Inclusion criteria

Training units that can provide at least four junior residents/registrars (postgraduate trainees) who have not yet been exposed to structured, formal EBM training and who will be available for the duration of the trial will be eligible. Brief descriptive characteristics of each participating junior postgraduate trainee will be collected.

Each institution needs to identify a 'facilitator' who will be able to work with the participants during the trial period. The facilitator will be someone working in the same department with the participants but will be a senior staff member preferably a specialist in obstetrics and gynaecology who is knowledgeable about basic EBM principles.

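### The main knowledge ANCOVA averages pre- and post-test scores over different sets of trainees once anyone drops out, and is biased if leaving depends on score differently in the two arms

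*Protocol article*

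**What the plan says.** Under Analysis plan, the protocol article states that "the analysis at the teaching unit will be the unit of analysis". Under Analysis plan for primary outcomes, each unit's summary is "the mean score for all the individuals taking the test in that unit at baseline (pre-) and post-evaluation phase". Knowledge, labelled there as the main outcome, is compared between arms "using analysis of covariance, with pre-test score as a baseline covariate and terms for the stratum and for the group in the model". Nothing limits the pre-test mean to trainees who also sat the post-test.

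A second analysis in the same section is built differently: "We will also compute the change in knowledge as the difference between the post- and the pre-test scores for each individual". These gains are averaged by unit and compared by analysis of variance. A gain needs both scores, so this analysis covers only trainees who sat both tests.

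The article states no drop-out rate and no rule for a trainee with one score. Inclusion criteria sets a minimum of four trainees per unit, "who will be available for the duration of the trial will be eligible". Data management adds that "any problems with logins, missing data and queries will be resolved promptly".

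**The concern.** Suppose weaker trainees leave before the post-test. The unit's post-test mean rises because of who remains, while its pre-test mean, still taken over everyone, does not move. The covariate cannot absorb the shift, so the model reads it as learning. If the shift is the same in both arms it cancels. If it is larger in one arm, the remainder enters the treatment effect.

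Arm-specific loss is plausible from the interventions described. Tables 1 and 2 give the experimental arm 20 hours of contact and make each module's assignment a condition for moving on. Table 4 times that arm's post-test from the end of the course. Table 3 gives controls no planned contact, and Table 4 times their post-test from baseline. Progress through the course can therefore affect who reaches the post-test in one arm only. In a unit of four, losing one trainee removes a quarter of those in the mean.

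**Working it through.** **The plan's own figure.** With 30 units per arm (1:1 assumed), a 10-point difference and a two-sided 5% test, power = Φ(10 / (SD·√(2/30)) − 1.96).

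- SD 10: Φ(3.873 − 1.96) = 97.2%
- SD 12: Φ(3.227 − 1.96) = 89.8%
- SD 14: Φ(2.766 − 1.96) = 79.0%

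The article states 97%, 90% and 80%. These reproduce, and this point does not touch them.

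**Inputs from the article.** 60 units, the 10-point difference, the two-sided 5% level, at least 4 trainees per unit, and the two definitions of the analysis.

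**Assumed inputs, not in the article.** m = 4 or 10 trainees per unit; within-unit SD 12 or 15 points; between-unit SD 8 at both tests, with the post-test unit effect equal to 0.6 times the pre-test one plus independent variation of SD 6.4; individual pre-post correlation ρ = 0.5; where leaving is selective, log-odds of leaving falling by 1 per within-unit SD of pre-test score. Stratum terms were left out.

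These variances fit the plan's own scale. They imply an SD of unit mean gain of √(0.16·64 + 0.64·64 + SDw²/m), with SDw the within-unit SD. This is 8.1 (m = 10, SDw 12) to 10.4 (m = 4, SDw 15), against the article's estimate of 7.9% and considered range of 5% to 15%.

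**Formula.** Let δ be the mean pre-test deviation of those who stay, in within-unit SDs, and D = SDw·(δ_exp − δ_ctl). With no true effect:

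- ANCOVA, means over all takers: bias ≈ ρ·D. The pre-test means are balanced by randomisation, so the covariate removes nothing.
- ANCOVA, both means over trainees with both scores: bias ≈ (ρ − b)·D, where b = (0.6·64 + ρ·SDw²/m) / (64 + SDw²/m) is the slope across units. Here b = 0.55 to 0.58.
- Gain ANOVA: bias ≈ (ρ − 1)·D, which is regression to the mean.

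Integrating the leaving model over a normal pre-test score gives δ = 0.119, 0.204, 0.277 and 0.346 at losses of 13%, 24%, 33% and 42%. For random loss δ = 0. For 33% v 13%, ρ·D = 0.5 × 12 × (0.277 − 0.119) = 0.95 at SD 12, and 1.19 at SD 15.

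**Simulation** (no true effect, 30 + 30 units, 1,500 runs per setting; ranges are over the four combinations of m and SDw):

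| Loss, experimental v control | ρ·D | All takers: bias | All takers: type I error | Both scores: bias | Gain: bias |
|---|---|---|---|---|---|
| 30% v 10%, random | 0 | -0.09 to +0.07 | 4 to 5% | -0.09 to +0.07 | -0.06 to +0.06 |
| 24% v 24%, same selection | 0 | -0.02 to +0.06 | 5 to 6% | -0.02 to +0.06 | -0.01 to +0.07 |
| 24% v 13%, weaker leave | 0.51 to 0.64 | +0.51 to +0.69 | 5 to 7% | -0.17 to -0.01 | -0.74 to -0.52 |
| 33% v 13%, weaker leave | 0.95 to 1.19 | +0.84 to +1.25 | 7 to 9% | -0.25 to -0.03 | -1.15 to -0.88 |
| 42% v 13%, weaker leave | 1.36 to 1.70 | +1.15 to +1.74 | 7 to 12% | -0.23 to -0.16 | -1.77 to -1.37 |
| 24% v 20%, selection in experimental arm only | 1.23 to 1.53 | +1.16 to +1.55 | 9 to 11% | -0.30 to -0.14 | -1.68 to -1.29 |

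The ANCOVA on trainees with both scores kept its type I error at 4 to 7% throughout.

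**Sensitivity.** With 8 trainees per unit, SDw 15 and about 33% v 13% loss, ρ = 0.3 gives +0.80 (all takers), -0.39 (both scores) and -1.57 (gain); ρ = 0.7 gives +1.71, +0.18 and -0.68. A separate run with 4 to 8 trainees per unit, between-unit SD 6, SDw 15 and 33% v 14% loss gave +1.2 points and 8.6% type I error for the all-takers ANCOVA.

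**The case against.** The strongest reply is that nothing in the article shows the harmful pattern will occur. Trainees must be available throughout, data entry is watched daily, and follow-up is about 12 weeks. No statement bars a trainee with unfinished assignments from the post-test. Control trainees have about 10 hours of study of their own and no facilitator to keep them engaged, so loss could be higher there. All of this stands: neither the amount nor the direction of loss is settled, and the sizes above are conditional.

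A reader might infer that unequal drop-out by itself biases the ANCOVA. It does not: random loss of 30% v 10% left every analysis unbiased. Conversely, similar rates can bias if selection operates in one arm only.

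It can also be said that the paired gain analysis already covers this, since gain is the outcome named under Outcome measures and used for power. It is a useful second view, but not a safeguard: the same selection biases it in the opposite direction.

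Another reply is that analysis sets are commonly left to an analysis plan that is not shown. Here, however, the article states who enters the means. The sentence could be read as trainees who sat the test at both phases, but that is the less natural reading, and one clause would settle it.

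**Conclusion.** The point holds in a conditional form. The stated rule lets covariate and outcome describe different trainees, and the two knowledge analyses cover different sets without saying so. Bias follows only if leaving is related to pre-test score and its rate or pattern differs by arm. It is then about +0.5 to +1.7 points when weaker trainees leave more in the experimental arm, with the sign reversed if they leave more in the control arm. That is 5 to 17% of the 10-point target: modest, but enough to take type I error to about 9 to 12% in the stronger scenarios. The drop-out rates, selection strength, variances and correlation are assumptions.

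A reader might go further and conclude that a unit-level primary analysis is unsound and must give way to an individual-level mixed model. The article does not support that. Analysing by teaching unit is valid for this cluster design, and matching the two means removes most of the bias. The mixed model's 8% smaller standard error (1.87 v 2.04 at equal 24% loss, against the all-takers ANCOVA) is a gain in efficiency, not the repair of an error.

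**What to change.** Under Analysis plan for primary outcomes, state that both the pre-test and the post-test unit means in the ANCOVA are computed over trainees with both scores, keeping the teaching unit as the unit of analysis. Report by arm the number lost between the tests and the pre-test scores of those who leave, so that readers can judge whether selection differed. An individual-level mixed model of post-test score on arm, own pre-test score, unit-mean pre-test score and stratum, with a random unit intercept and small-sample degrees of freedom, can be added as a sensitivity analysis.

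The cost is a clause and a short table, from data already collected. Trainees with only one score drop out of the main ANCOVA. The residual bias was about 0 to -0.4 points in most settings, and +0.2 at the highest correlation tried. Neither this change nor the mixed model corrects drop-out that depends on unobserved post-test scores.

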### Number of subjects and statistical power

There is limited information regarding baseline EBM knowledge and possible knowledge gains and practice changes following implementation of such courses [16]. The evaluation of the pilot course developed within the Leonardo da Vinci pilot project provided some data that were used in the sample size calculation [6,7]. In the pilot evaluation only electronic modules were evaluated as a before and after analysis: For sample size calculations, the standard deviation (SD) for the average gain in knowledge (%) estimated from teaching units/modules means in different countries as SD = 7.9% (likely to be an overestimate) was taken. To allow for random variation of this estimate, a range of SD between 5% and 15% was considered. The power achieved with a total of 60 teaching units to detect a difference in gain of 10% (relative to the maximum score) between two groups in a two-sided test of 5% level, assuming SD = 10%, is 97%. If SD = 12%, the power is 90%. If SD = 14%, the power is 80%. Seven countries: Argentina (4 institutions), Brazil (20), Democratic Republic of Congo (4), India (10), Philippines (10), South Africa (6), Thailand (10) will participate in the trial whose duration is estimated in one year.

## Main problems anticipated

**Identification of facilitators**in the experimental intervention units: The principal investigator will use her/his judgement on the selection of the facilitators and provide training if appropriate. However, the whole philosophy of the Course is for the facilitators to guide the students in the clinical setting and monitor their progress in the process. The facilitators do not need to be EBM experts but rather respected clinicians that could be seen as role models or opinion leaders within their settings.

### Internet connectivity

Although all settings will have access to internet for data entry and course content (RHL-EBM) our initial contacts suggest that there may be connectivity problems in some settings like Congo DRC and South Africa. In these settings close monitoring by principal investigators will be required to ensure that emerging problems are solved rapidly.

### Existing EBM courses

It is possible that in some of the teaching units there may be other postgraduate teaching activities such as workshops or scientific conferences. It is not possible to control these activities occurring in each setting. The survey conducted before the trial will give information on the scope of the activities likely to exist in each setting. There are two possible protective mechanisms against these activities becoming a threat to the validity of trial results. First, random allocation should ensure that such activities are equally distributed in both groups. Second, stratified analysis based on the presence and absence of existing courses is planned as a secondary analysis.

## Expected outcomes of the study

If effective, the RHL-EBM Course will provide an educational intervention that can be scaled up in low and middle-income countries in both teaching and non-teaching institutions. As such it will form a core component to improve quality of care. Discussions with national and international professional organizations to implement the course with formal certification can be performed.

Improvements on knowledge gain, attitudes and skills are important for providing good quality care. Any potential impovement in educational environment will have a major impact on the quality of inservice training not only in resource-poor settings. An original EBM Educational Environment Measurement Tool will be available for all academic or nonacademic settings.

Trial results will be published in a peer-reviewed journal. The results will be disseminated to the participating centres through meetings of the research team with participants at the end of the study. The results will also be presented and disseminated through the WHO website and the WHO reproductive Health Library (RHL).

## Ethics and informed consent

The trial interventions are implemented at the institutional level. Therefore, the primary point at which permission is sought is at the institutional level. Receiving permission from the institution does not constitute a consent on behalf of the participants. It constitutes an administrative agreement between the PI and the institution. A permission sheet will be presented to the person responsible for the institution to be signed. We anticipate that in most cases this person will be the academic head of the obstetrics and gynaecology department.

The facilitators/focal persons and the postgraduate trainees will be informed that one or more educational programme(s) are being evaluated but with no further details. After random allocation each unit will be informed about the activities they should follow including completion of MCQs and other online assessments. We plan to seek consent from individuals within the participating institutions. Individuals will not be identified in the questionnaire. If *intervention 1 *is shown to be beneficial in the primary endpoints then it will be provided to all *intervention 2 *institutions.

The study protocol was ethically aproved by WHO and will also be aproved in each participatin g country.

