### Recruitment and allocation

The training institutions (clusters) identified by the principal invstigators and fulfilling the inclusion criteria will be asked to participate in the trial. The random allocation scheme will be generated at HRP/RHR using computer-generated random numbers. Each cluster will be allocated to either of two groups: RHL-EBM course (intervention 1) or passive dissemination of EBM teaching materials (intervention 2). Due to the nature of the intervention and design it will not be possible to blind the research teams or the participants of their allocated group. However, the participants will only be informed about an educational programme evaluation and will not be told which groups are compared. The individual trainees will receive similar information on a written information sheet.

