**Table 4 T4:** Intervention and control group

	Experimental group	Control group
**Before**	Introduction and consent MCQs M1-M5 Attitude questionnaire Educational environment measurement tool	Introduction and consent MCQs M1-M5 Attitude questionnaire Educational environment measurement tool

**Implement interventions**	•RHL EBM course over maximum 8 weeks (5 modules, completion of assignments for each module/week) •Current local teaching	•RHL and workshop-based course materials handed out to each participant •Current local teaching

**Assessment**	•MCQs: 3-4 weeks after the end of the course •Attitudes: questionnaire 3-4 weeks after the end of the course •Competencies: OSCE 4 weeks after the end of the course •Educational environment: 4 weeks after the end of the course	•MCQs: 12 weeks after baseline assessment •Attitudes: 12 weeks after baseline assessment •Competencies: OSCE 12 weeks after baseline assessment •Educational environment: 12 weeks after baseline assessment

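### Nothing places trainee listing, consent or the baseline tests before a unit learns its arm, so enrolment and baseline performance can differ by arm

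*Protocol article*

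**What the plan says.** Randomisation is by training institution: "Each cluster will be allocated to either of two groups" (Recruitment and allocation). The same section concedes that "it will not be possible to blind the research teams or the participants of their allocated group".

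On timing, Ethics and informed consent says: "After random allocation each unit will be informed about the activities they should follow including completion of MCQs and other online assessments". The next sentence reads "We plan to seek consent from individuals within the participating institutions" and carries no time marker. Table 4 puts "Introduction and consent MCQs M1-M5 Attitude questionnaire Educational environment measurement tool" in its first row, headed Before, with the same entry for both arms.

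There is some masking. Recruitment and allocation says "the participants will only be informed about an educational programme evaluation and will not be told which groups are compared". Ethics and informed consent says facilitators and trainees "will be informed that one or more educational programme(s) are being evaluated but with no further details".

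Inclusion criteria requires a unit to be able to supply at least four eligible trainees, but mentions no list of names fixed before allocation. Table 2 has the MCQ supervised by the tutor or someone the tutor names, and opens the e-learning only once the pre-test is done. Table 3 likewise gives controls their slides after the baseline assessment.

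The Analysis plan for primary outcomes uses the pre-test twice: as the covariate in an ANCOVA on unit means, and in each trainee's post-minus-pre gain.

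**The concern.** Randomising clusters protects the comparison of units. It protects the comparison of trainees only if they were identified and enrolled without knowledge of the arm. Here individuals consent, the outcomes are measured on individuals, and the one sentence that fixes a time has units learning their activities after allocation.

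Those activities differ visibly. Table 1 gives the experimental course 20 hours in total with facilitator contact, assignments and assessments, plus 2 to 3 hours of e-learning. Table 3 gives the control about 10 hours of self-directed learning and no planned contact. A head of unit or facilitator who knows which package is coming can influence which trainees are put forward, and a trainee who knows the workload may decide differently.

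Two things are at stake. If keener trainees enrol in one arm, any of the outcomes can be shifted. If effort at the pre-test depends on arm, the covariate and the gain score both carry that dependence into the treatment estimate. No later analysis can fully repair either.

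**Working it through.** **1. What the text fixes and what it leaves open**

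| Step | Where | Timing relative to the unit learning its arm |
|---|---|---|
| Cluster recruited and allocated | Recruitment and allocation | Before |
| Unit told its activities, including the MCQs | Ethics and informed consent | This is the disclosure |
| Trainees given neutral information | Recruitment and allocation; Ethics and informed consent | Not stated; mentioned just before the disclosure sentence |
| Individual consent | Ethics and informed consent; Table 4 | Not stated; mentioned just after the disclosure sentence |
| Baseline MCQ, attitude questionnaire, EBMEEM | Tables 2 and 4 | Not stated outright; the pre-course MCQs are the first MCQs a unit completes, so the natural reading is after |

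No step involving named trainees is placed before disclosure.

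**2. The plan's power figures, to obtain the standard error**

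Inputs from Number of subjects and statistical power: 60 units, a 10-point difference in gain, two-sided 5%. Equal allocation, 30 per arm, is my assumption.

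SE = SD × √(2/30); power ≈ Φ(10/SE − 1.96).

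- SD 10: SE = 2.58, power 97.2% (stated 97%).
- SD 12: SE = 3.10, power 89.8% (stated 90%).
- SD 14: SE = 3.61, power 79.0% (stated 80%).

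The stated figures reproduce to within about a point.

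**3. How a shift reaches the estimate**

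Let β be the ANCOVA slope on the pre-test. The ANCOVA effect is (difference in post-test means) − β × (difference in pre-test means). The gain analysis is the same expression with β = 1.

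- *Baseline effort only.* The experimental pre-test is lower by d and the post-test is unaffected. Bias is d in the gain analysis and βd in the ANCOVA. For d = 3: 3 points, and 0.3 × 3 = 0.9 to 0.7 × 3 = 2.1 points.
- *Enrolled trainees differ by a constant e at both tests.* Bias in gain is e − e = 0; in the ANCOVA it is (1 − β)e. For e = 3 and the same slopes: 0.3 × 3 = 0.9 to 0.7 × 3 = 2.1 points.
- *Enrolled trainees would gain g more under either package, with equal pre-tests.* Bias is g in both analyses.

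The values of d, e, g and β are assumptions; the documents supply none of them.

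**4. Effect on the test of gain**

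With no true effect and a spurious arm difference b in gain, the rejection probability is 1 − Φ(1.96 − b/SE) + Φ(−1.96 − b/SE), with 30 units per arm:

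| b (points) | SD 7.9 | SD 10 | SD 14 |
|---|---|---|---|
| 0 | 5.0% | 5.0% | 5.0% |
| 1 | 7.8% | 6.7% | 5.9% |
| 2 | 16.5% | 12.1% | 8.6% |
| 3 | 31.3% | 21.3% | 13.2% |
| 5 | 68.8% | 49.1% | 28.2% |

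The SD of 7.9 is the pilot value quoted in the article; 10 and 14 are from its power statement.

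**The case against.** The strongest reply is that the article never says consent follows disclosure. The consent sentence has no date, and the sentence just before the disclosure sentence has facilitators and trainees receiving neutral information, which could come first. Table 4 lists consent under each arm only because its columns are arms. The sentence about MCQs covers post-tests as well as pre-tests. The pool is small: first- and second-year trainees in units already surveyed. Neither arm's materials open until the baseline is complete, so teaching cannot contaminate the pre-test. A condensed article may also leave the detailed consent sequence to the full protocol.

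Much of this stands. The consent order is an inference, and what remains at baseline is motivation or effort, not prior exposure to the materials. It does not dispose of the point. The article does give a sequence, and the only step it dates is disclosure after allocation. Neutral wording hides the comparison from trainees; it does not hide a unit's own activities from its staff, and the article concedes that research teams cannot be blinded.

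A reader might also infer that facilitators are chosen once the arm is known, because Main problems anticipated discusses them for experimental units and says "The principal investigator will use her/his judgement on the selection of the facilitators and provide training if appropriate". Inclusion criteria, however, makes naming a facilitator a condition for every institution. The two sections need reconciling; they do not show selection after allocation.

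**Conclusion.** The point holds as a risk that the stated procedure leaves open. It is not a demonstration that enrolment will be biased. The plan tells units their activities after allocation and contains nothing that puts trainee listing, consent or baseline testing ahead of that.

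The size cannot be derived from the documents. Under the stated assumptions, a baseline-only shift of 3 points biases the gain analysis by 3 points and the ANCOVA by 0.9 to 2.1. A spurious 2- to 3-point difference in gain raises the false-positive rate from 5% to about 12% to 21% at SD 10. The direction is not known either.

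A reader might be tempted to set a raw-score difference between those who enrol and those who decline directly against the 10-point target. That does not follow: the target is a difference in gain, and a difference present equally at both tests cancels from the gain. It matters there only if enrolment is related to how much a trainee would gain, or if effort at the pre-test changes.

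**What to change.** State and follow this order for every unit:

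1. The unit lists its eligible trainees by name.
2. Those trainees consent on the neutral information already planned.
3. They complete the baseline MCQ, attitude questionnaire and EBMEEM online.
4. Only then does the coordinating centre release that unit's allocation.

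Trainees added after release are excluded from the primary analysis. Report the numbers eligible and consenting by arm. If this is already the intended practice, saying so in Recruitment and allocation and in Ethics and informed consent is enough. Separately, reconcile Inclusion criteria with Main problems anticipated on when facilitators are named.

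The allocation scheme can still be generated in advance; only its release waits. The online system already holds back materials until the baseline is complete, so the extra cost is a short delay before each unit starts. No sample-size figure changes. The change has to be made before enrolment, because the bias cannot be removed afterwards.
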